## Abstract

**Introduction:**

The individual, societal and economic benefits of stroke prevention are high. Even though most risk factors can be reduced by changes to lifestyle habits, maintaining new and healthy activity patterns has been shown to be challenging.

The aim of the study is to evaluate the impact of an interdisciplinary team-based, mHealth-supported prevention intervention on persons at risk for stroke. The intervention is mediated by engaging everyday activities that promote health. An additional aim is to describe a process evaluation that serves to increase knowledge about how the programme leads to potential change by studying the implementation process and mechanisms of impact.

**Methods and analysis:**

The study will be a randomised controlled trial including 104 persons at risk for stroke. Persons at risk of stroke (n=52) will be randomised to an mHealth-supported stroke prevention programme. Controls will have ordinary primary healthcare (PHC) services. The 10-week programme will be conducted at PHC clinics, combining group meetings and online resources to support self-management of lifestyle change using engaging everyday activities as a mediator. Primary outcomes are stroke risk, lifestyle habits and participation in health-promoting activities. Assessments will be performed at baseline and at follow-up (11 weeks and 12 months). The effects of the programme will be analysed using inferential statistics. Implementation will be analysed using qualitative and quantitative methods.

**Ethics and dissemination:**

The study has been approved by the Swedish Ethical Review Authority. Study results will be disseminated in peer-reviewed journals and at regional and international conferences targeting mixed audiences.

**Trial registration number:**

NCT05279508.

STRENGTHS AND LIMITATIONS OF THIS STUDYA robust randomised controlled trial design will be used to investigate the effectiveness of the intervention programme.A process evaluation will provide rich data, useful for analysing the outcomes and the research process.A limitation is that primary outcomes are based on self-reported data.An inclusion criterion is motivation for change, which can skew the results and lower external validity.

## Introduction

In Sweden, a healthcare reform programme entitled ‘Good Quality Local Health Care— A Primary Care Reform’^1^ is currently paving the way for a large-scale transformation. The reform targets primary healthcare (PHC) specifically and is designed to proactively address and prevent illness at an early stage to reduce the burden of non-communicable diseases (NCDs), such as stroke. The reform is in line with the United Nations Sustainable Development Goals, urging governments to reduce premature mortality from NCDs by 1/3 by the year 2030 through prevention and treatment.^2^ By the age of 55, the risk for stroke increases considerably and doubles each decade afterward.^3 4^ Although the incidence of stroke has decreased in the general population, trends show an increase in stroke incidence in young adults.^5^ In Sweden, stroke incidence has declined by over 40% in the last 15 years.^6^ However, both globally and in Sweden, cerebrovascular diseases such as stroke continue to be the most common cause of death and impairment.^7^

The individual, societal and economic benefits of stroke prevention are high. Many of the stroke risk factors are largely addressable; for example, smoking, obesity, type 2 diabetes, hypertension, physical inactivity and dietary intake. The benefits of a healthy lifestyle are clear^4 8^; however, the long-term effect (follow-up at 12 months or longer) of lifestyle interventions is not.^9 10^ For example, the effectiveness of PHC-based physical activity interventions is inconclusive.^11^ There is evidence for short-term improvements, but there is a lack of evidence for long-term effects.^9^ A multifactorial approach to stroke prevention is warranted. A systematic review showed that multifactorial lifestyle habit interventions have a greater potential effect on reducing risk factors than single-factor interventions.^12^ Preliminary evidence exists from a Swedish trial on a multifactorial lifestyle counselling programme^13^ that improved physical activity and dietary habits and reduced smoking and stress; however, the study was not conducted in PHC and did not have a control group. mHealth (a term for the combination of eHealth services and smartphone technology^14^) presents possibilities for accessibility and affordability when developing health services^15 16^ making it an excellent tool for designing stroke prevention models.^17^

### Theoretical concept of the intervention programme

The programme is a complex intervention, and the Medical Research Council (MRC) guidance for developing and evaluating complex interventions^18^ has been used in the design of the study. MRC suggests several key elements and stages; development, feasibility/piloting, evaluation and implementation. This randomised controlled trial (RCT) evaluates the effectiveness and implementation of the Make My Day (MMD) programme and is based on already-completed or ongoing studies concerning development and feasibility.

#### Engaging everyday activity

In the MMD programme, engaging everyday activities (EEA) are seen as the means and goal for changing and sustaining a healthy lifestyle in the intervention programme, and while it is not a new concept, it has not been studied in relation to changing lifestyle habits to prevent NCDs. EEA is defined as a special type of activity, that is, based on individual experience, filled with meaning and gives a sense of intense participation and enthusiasm to the individual.^19 20^ Examples from previous studies show that EEA can include a variety of activities such as working, playing computer games and reading books. We recently showed that an intervention programme targeting cardiovascular disease prevention could benefit from incorporating health promoting EEA.^21^ The complexity of changing lifestyle habits has been described as a paradox between EEA and health.^22^ Even though EEA is subjectively meaningful and engaging to an individual, it might have an arguably negative impact on health; for example, engagement in sedentary activity or in unhealthy behaviours.^22^ In the current project, EEAs are seen as having the potential to change everyday activity patterns, and when carefully designed (eg, listening to an audiobook while taking a walk), incorporate a routine that promotes sustainable health among persons at risk for stroke. Studies have shown that promoting EEAs can have positive health impacts on older adults.^23–25^ Studies on populations that live lives that incorporate EEAs combined with moderate-intensity physical activities and a healthy diet indicate a strong relation to well-being, longevity and cultural context.^4 5^

The current state-of-the-art in stroke prevention suggests the need for a multifactorial PHC intervention that addresses modifiable risk factors for stroke based on individual needs and engagement in everyday activities that promote health with the support of a mHealth service.

### Objectives of the proposed study

The main aim of the study is to evaluate the impact of an interdisciplinary team-based, mHealth-supported prevention intervention in PHC—mediated with EEAs that promote health—to decrease stroke risk (primary outcome), and increase participation in EEAs and health-related quality of life (HRQoL). The aim is also to describe a process evaluation that serves to increase knowledge about how the programme leads to potential change by studying the implementation process and mechanisms of impact.

### Hypothesis

We hypothesise that the MMD intervention programme is more beneficial than regular PHC services (control group) in decreasing stroke risk (primary outcome). We also hypothesised that MMD is more beneficial than regular PHC in increasing (a) participation in health promoting EEAs and (b) HRQoL.

## Methods and analysis

### Design

The study will be a randomised, assessor-blinded, controlled trial of persons at risk for stroke. The process evaluation answers questions as to what interventions were delivered and how by combining qualitative interviews and descriptive quantitative data on the implementation, causal mechanisms and contextual variation.^26^

### Study setting

The study will be conducted in close collaboration with four PHC clinics in the Stockholm area (different parts of Stockholm to represent a diversity in geographical area). PHC clinics in this study are rehabilitation units involving dietitians, physiotherapists and occupational therapists. In Region Stockholm, rehabilitation units are often both organisationally and geographically separate from general practitioner (GP) PHC clinics. These PHC rehabilitation units have an agreement with the County Council in Stockholm and are available for patients to choose from without the need of a referral for treatment by certified physiotherapists, occupational therapists and dieticians. PHC services are publicly funded in Sweden.

### Sample size and power considerations

The primary outcome is stroke risk, with emphasis on modifiable stroke risk factors. Based on data from a case study,^27^ we calculate a decrease of at least one level of stroke risk (eg, moving from high risk to medium risk in the Stroke Risk Score Card^28^) with an SD of 1.5, the statistical power of 80%, with two-tailed α=0.05. Under these assumptions, the required sample size was 35 in each group (in total n=70). The Stroke Risk Scorecard was developed as an easy-to-use self-assessment tool by the National Stroke Association in the UK.^28^ The tool has been used previously in a few studies to detect risk factors of stroke^27 28^ and in a recently finished pilot study conducted in the research group (publication in manuscript). Since the Stroke Risk Scorecard has not been sufficiently tested psychometrically, power calculations were added for performance in EEAs. Assuming a difference on performance in EEAs of two points (as measured with the Canadian Occupational Performance Measure (COPM)^29^) a power of 0.8 and a two-sided p value of 0.05 a sample size of 40 participants in each group would be sufficient.

To safeguard against drop-outs (a maximum 30% drop-out rate is assumed), a total of 104 participants will be enrolled in the study (52 in each group).

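### Enrolling 104 keeps the 40 per group given for the secondary COPM calculation only up to about 23% drop-out, not the stated 30%; the primary-outcome requirement is still met

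*Protocol article*

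**What the plan says.** All the figures stand in the protocol article under Sample size and power considerations.

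- **Primary outcome (Stroke Risk Scorecard).** The target is one risk level: "we calculate a decrease of at least one level of stroke risk", "with an SD of 1.5, the statistical power of 80%, with two-tailed α=0.05". The result is "the required sample size was 35 in each group (in total n=70").
- **COPM.** This calculation was added because the Scorecard lacks sufficient psychometric testing: "Assuming a difference on performance in EEAs of two points", with "a power of 0.8 and a two-sided p value of 0.05 a sample size of 40 participants in each group would be sufficient". No SD is given. Table 2 and the Outcome data section class COPM as a secondary outcome, and the Discussion describes the added calculation in the same way.
- **Drop-out.** The allowance and the enrolment are given together: "a maximum 30% drop-out rate is assumed), a total of 104 participants will be enrolled in the study (52 in each group"). The inflation formula is not shown, and the text does not say which of the two calculations the 104 was built on.

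The Participant timeline section reports that all 104 had been included by June 2023. The Data analysis plan specifies analysis of covariance with the baseline value as covariate for continuous outcomes.

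**The concern.** Three stated figures do not fit together: 40 per group as the number for COPM, 30% as the maximum loss, and 52 per group enrolled. An allowance for a maximum loss should still deliver the target number when that loss occurs. Here it does not for COPM.

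The likely cause is a common slip. To end with n evaluable participants after losing a fraction d, one enrols n/(1 - d). Enrolling n x (1 + d) falls short, because the loss applies to the larger enrolled number.

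At stake is the drop-out tolerance that the protocol claims for its supporting calculation. COPM is there to offset an acknowledged weakness of the Scorecard, and the Discussion itself raises the risk that less motivated participants will leave. If the sentence stands, a 30% tolerance that the numbers do not support could be carried into the results report.

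**Working it through.** **Inputs** (all from Sample size and power considerations): Scorecard difference 1, SD 1.5, 35 per group; COPM difference 2, no SD, 40 per group; power 80% and two-sided 0.05 for both; drop-out 30%; enrolment 104 (52 per group).

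**1. Reproducing the 104.**

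| Base | x 1.3 | ÷ 0.7 |
|---|---|---|
| 70 (Scorecard, 2 x 35) | 91 | 100 |
| 80 (COPM, 2 x 40) | **104** | 114.3 |

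Only 80 x 1.3 gives 104, and it does so exactly (40 x 1.3 = 52 per group). That this formula was used is an inference from the match. Step 2 does not depend on it.

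**2. What 104 delivers at 30% loss.**
- Remaining: 104 x 0.7 = 72.8, or 52 x 0.7 = 36.4 per group, against 40.
- Largest loss that leaves 80: 1 - 80/104 = 23.1%.
- Enrolment that would have left 40 per group: 40/0.7 = 57.1, so 58 per group or 116 in total, 12 more than 104.

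**3. Primary outcome.**
- Stated requirement: 70/0.7 = 100, below 104. About 36 per group remain, against 35.
- Rebuilding the 35 by the normal approximation: n = 2 x (1.96 + 0.8416)² x (1.5/1)² = 35.3, which rounds up to 36. The t-test gives 36.3. The stated 35 is reproduced to within about one participant.
- Power at 36 per group: 80.7% (normal), 79.7% (t-test). So about 80% is kept, with essentially no reserve.

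**4. COPM power at 36 per group.** With no SD stated, it has to be back-calculated. If 40 per group gives exactly 80% power, then:
- Normal: d = (1.96 + 0.8416) x √(2/40) = 0.626, so SD = 2/0.626 = 3.19.
- t-test: d = 0.634, so SD = 2/0.634 = 3.15.
- Power at 36 per group: 75.7% (normal), 75.6% (t-test).

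The result depends on the SD. By two-sample t-test:

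| Assumed COPM SD | n per group for 80% | Power at 36 per group |
|---|---|---|
| 2.5 | 25.5 | 91.7% |
| 3.0 | 36.3 | 79.7% |
| 3.15 | 39.9 | 75.7% |
| 3.2 | 41.2 | 74.4% |

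**5. Baseline adjustment.** If the baseline-outcome correlation is r, ANCOVA raises the effective d to d/√(1 - r²). With d = 0.634 and 36 per group, r = 0.3 gives 79.5% and r = 0.4 gives 82.5%. The documents state no correlation, so both values of r are assumptions.

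**The case against.** The best case on the other side is that little depends on this.

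- **It touches only a secondary outcome.** This stands. A reader might infer from the shortfall that the trial has lost its primary-outcome power. The documents do not support that: 35 per group is the stated primary requirement, and 104 covers it at 30% loss.
- **The text never says that 104 protects both calculations.** This also stands. It says only that 104 allows for drop-out, and it calls 40 per group sufficient for COPM, reserving the word required for the 35. The stronger reading, that the protocol promises 80% COPM power at 30% loss, is not written there. Still, the 104 can be derived only from the COPM figure, and a reader will naturally take the allowance to apply to the calculation just before it.
- **30% is a maximum, not an expectation.** This limits the practical effect, since there is no shortfall up to about 23% loss. It does not repair the sentence, because an allowance for a maximum should hold at that maximum.
- **The planned ANCOVA may recover the power.** Possibly, as step 5 shows. But the sample size section invokes neither adjustment nor a correlation, so its figures cannot rest on one.
- **The 76% is conditional.** This is correct. If 40 was rounded up or chosen conservatively, the SD is smaller and the power at 36 higher. The 23% limit and the 36 per group need no SD.

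**Conclusion.** The figures are inconsistent as written. With 104 enrolled and 30% lost, about 36 per group remain, against the 40 given for 80% COPM power. The enrolment keeps 40 per group only up to about 23% drop-out. Both results follow from stated figures alone. That the cause is multiplication by 1.3 is a strong inference from an exact match, not something the protocol states.

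The size is modest: a loss of about 4 power points, from 80% to about 76% unadjusted, on a secondary outcome and only at the assumed maximum drop-out. That figure rests on an SD of about 3.15, which assumes that 40 is the exact requirement by two-sample t-test. The primary outcome keeps about 80% power at 30% loss, so this is not a finding that the trial is underpowered for its main question. Severity is moderate to minor.

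**What to change.** Enrolment is complete, so the remedy is a change of wording under Sample size and power considerations:

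1. State that 104 enrolled retains 40 per group for COPM up to about 23% drop-out, and that at 30% about 36 per group remain. Lead with this, since it needs no further assumption.
2. State that the primary-outcome requirement of 35 per group is still met at 30%, with about 80% power.
3. Give the COPM SD that was used and the unadjusted COPM power that follows at 36 per group. This is about 76% if the SD is near 3.15, and should be recalculated if it is not.
4. If power is restated for the baseline-adjusted ANCOVA, give the baseline-outcome correlation and label it as an assumption.

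The cost is a few sentences. No participants are added and no analysis changes. The stated drop-out tolerance for COPM becomes somewhat less favourable.

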### Participants: recruitment and eligibility criteria

Persons at risk of stroke will be included in the project and participants will be recruited via advertisements in social media, a webpage and flyers at PHCs. A stroke risk online screening survey will be used to find eligible participants. Inclusion criteria for the study are (a) three or more risk factors deemed ‘high risk’ using the Stroke Risk Scorecard, (b) motivation for lifestyle change and to participate in a digital lifestyle intervention (including use of a smartphone) and (c) aged between 55 and 75 years old, and without a diagnosis of dementia or cognitive impairment hindering participation. Exclusion criteria include having previously had a stroke or a transischaemic attack diagnosis, lack of understanding of the Swedish language and not being able to use a mobile phone application. A total sample of n=104 participants (persons at risk of stroke), divided into two arms (52+52) for intervention and controls is estimated. Block randomisation will be used with a block size of 4.^25^ Allocation will be done following baseline assessment by a researcher not involved in data collection or intervention. The assessors of outcomes will be blinded to allocation until the end of the study.

In addition, next of kin to persons at risk for stroke in the intervention group are also invited to answer questions (survey and interview) regarding support of their relative. Persons at risk for stroke who do not have a next of kin will not be excluded from the study. PHC professionals who have been trained and delivered the intervention programme will be additional participants in the process evaluation of the study. Stakeholders (such as leaders at the involved PHC clinics) will be invited to individual interviews.

### Informed consent

Written informed consent will be obtained from all participants (persons at risk, their next of kin, and PHC staff and stakeholders) at the start of recruitment. Information about the study will be given in written and verbal forms during meetings with research staff. Persons at risk will be asked to identify a next of kin that will be asked to participate by the researchers.

### MMD: a stroke prevention programme

The MMD intervention programme enables healthy activity patterns and aims to reduce the risk of stroke by means of four strategies: (a) the incorporation of health-promoting EEAs, (b) the use of mobile phone technology (mHealth) to increase health literacy, and awareness of current habits and fostering self-management, (c) setting realistic goals that form new habits that prompt conscious decisions for healthy choices and habits and (d) sharing experience in a learning environment.

### Duration and specific content of the intervention programme

The MMD stroke intervention programme is a 10-week group programme consisting of five sessions over the first 5 weeks, followed by a sixth booster session 5 weeks later. During the intervention, participants will work actively on self-chosen goals, EEAs and habits to change behaviour and lifestyle. A mobile phone app will be used by participants throughout the 10 weeks, supporting their awareness of current lifestyle habits and everyday activities. To form new habits, common situations will be used to cue behaviour change, like seeing an elevator and looking for the staircase, prompting health-promoting behaviour and making a conscious decision to walk the stairs.^30^ The continuation of a change process is expected from the participants following the 10-week programme period, and strategies for self-management are anticipated.

Each session (90 min) has a theme and includes some type of activity such as exercise, making a light snack or taking a walk. Group dynamics and personal experience are used to reflect on EEAs in relation to health, doing and future goals. The sessions and content, presented in table 1, are delivered by a trained health professional, for example, an occupational therapist, physiotherapist or dietician. There are sessions weeks 1–5 and week 10. During weeks 6–9, no sessions are held, instead the participants are expected to self-manage these weeks with the support of a mobile phone app.

**Table 1 T1:** Summary of session themes, concepts and activities supporting a change process

Week	Session theme	Profession	Concepts	Activity
1	1: Risk factors for stroke and engaging everyday activities	Occupational therapist	Health literacy concerning stroke risk, engaging activities, change process, expectations	Peer interview on engaging activities. Learn how to register in the app
2	2: Physical activity	Physiotherapist	Physical activity, physical inactivity	Try a physical group exercise class at a gym
3	3: Diet and health	Dietician	Dietary routines and change	Food lab—prepare and test; for example, healthy snacks/sandwiches
4	4: Balanced everyday life	Occupational therapist	Activity balance and stressors	Relaxation—such as medical yoga or meditation
5	5: The meaning of healthy habits, routines and activity patterns	One of the team members	Current and desired routines/habits, activity patterns and resources	Walk-and-talk—for example, in a forest or a historical walk in the city
10	6: Booster session: evaluation and the road ahead	Occupational therapist	Self-management, sustainability, view of the self, social support, revisiting goals/new goals and social aspects of health	Preparing healthy snacks and group reflection on the programme

The healthcare professionals who will provide the MMD programme/intervention will participate in structured education specially designed for this programme. This education will be given in an on-site and digital combination on three occasions and will be held by two research team members with extensive experience in pedagogy and in the research protocol. In addition, the health professionals will have access to a digital educational platform with rich and varied material, and all material to be used during the 10-week programme. To avoid contamination, the health professionals are instructed to not deliver the 10-week programme to other patients during the research period.

